## Abstract

**Supplementary Information:**

The online version contains supplementary material available at 10.1186/s40337-025-01358-z.

## Introduction

Impaired inhibitory control and disinhibited eating is predominantly seen in a subgroup of individuals with overweight and obesity suffering from regular binge eating behaviours. Binge eating according to DSM-5 is defined as eating a large amount of food accompanied by a subjective loss of control [4]. Transdiagnostic approaches suggest that individuals with regular binge eating, regardless of specific eating disorder diagnoses, represent a shared clinical entity. Regular binge eating is the primary symptom in Binge Eating Disorder (BED), Bulimia Nervosa (BN), and in Other Specified or Unspecified Feeding and Eating Disorders (OSFED/UFED) with regular binge eating behaviour [40, 42, 54]. Impairments in inhibitory control are considered a vulnerability factor linked to disinhibited eating patterns and, as a consequence, weight gain and difficulties in weight regulation [21]. These vulnerabilities highlight important targets for tailored interventions and treatment strategies.

### The role of inhibitory control in binge eating

Inhibitory control refers to the ability to suppress dominant reaction in favour of another reaction [39]. It enables individuals to act on intentions that conflict with habits, motivations, or competing goals [22]. One important process to achieve inhibitory control consists in top-down focusing on relevant stimuli while ignoring irrelevant stimuli [36]. Deficits in inhibitory control are considered a vulnerability factor for obesity and binge eating [12, 18, 21, 43]. If food stimuli are perceived as highly rewarding, they attract a strong attentional focus and if inhibition mechanisms fail, overeating may occur [15, 20].

### Underlying neurobiological markers and their implementation in inhibitory control trainings

The prefrontal cortex and especially the dorsolateral prefrontal cortex is closely linked to inhibitory control processes [14] and plays a key role in processing food stimuli [17]. Current evidence highlights the dorsolateral prefrontal cortex’ central role in the regulating eating behaviour, and especially in inhibitory control [20, 28, 29, 32]. Its activation during both short- and long-term attempts to resist food intake makes it a promising target for modulating inhibitory control over eating. One approach is inhibitory control training (ICT) [43], such as the antisaccade paradigm, where participants are instructed to avert their gaze as soon as a stimulus is shown, therefore demanding a suppression of an undesirable but highly dominant behaviour and initiating and executing an alternative behaviour [27]. This training approach recently proved to be feasible and acceptable in a clinical eating disorder population, improving inhibitory control towards high-caloric food images and a reducing binge eating frequency [19]. These effects were enhanced by application of transcranial direct current stimulation (tDCS) of the right dorsolateral prefrontal cortex, supporting the central neuropsychological involvement of neural circuits in inhibitory control [19, 38].


### Study aims

Multiple aspects should be addressed to advance our understanding of eating disorders. First, existing treatments for individuals affected by binge eating often lack both effectiveness as well as long-term impact, highlighting the need for novel therapeutic approaches. The current trial targets underlying neurobiological mechanisms, particularly inhibitory control, which appears to be a key factor in the development and maintenance of binge eating behavior. This is directly addressed through ICT. Moreover, we examine the role of feedback, a critical component in modulating motivation and its influence on treatment outcomes. In particular, we investigate non-inferiority of ICT without feedback compared to CT with feedback; inferiority of ICT compared to WL. Finally, given that the mechanisms behind effective treatment are still not fully understood, we aim to identify predictors and moderators of treatment success. This will support the development of individualized treatment strategies—not only by deepening our understanding of the core mechanisms that contribute to treatment response or even remission, but also by informing the implementation of these strategies into scalable, app-based self-guided interventions.

### Current study

As the food-modified antisaccade training alone produced strong effects in our previous trial [19], including decreases of binge eating frequency, eating disorder pathology, and antisaccade performance independently from the tDCS condition, we now investigate mechanisms underlying the effects of the food-modified antisaccade training without neuromodulatory support through tDCS. This proof-of-principle trial will investigate the role of feedback in the food-modified antisaccade training to reduce binge eating. In a randomized controlled parallel group design two conditions of the inhibitory control training are implemented: a) with feedback and b) without feedback. Both will be compared to c) no treatment. The superordinate research question of the project is to investigate the role of feedback in the food-modified antisaccade training to reduce regular binge eating behaviours. In more detail, we propose:Noninferiority of the food-related antisaccade training without feedback compared with the original training including feedback in patients with regular binge eating regarding binge eating frequency (primary outcome) and eating disorder pathology, impulsivity, task performance, motivation and self-efficacy (secondary outcomes).Confirmation of clinically relevant effects of the training without feedback against the waitlist control and confirmation of clinically relevant effects of the training with feedback against the waitlist control i.e. superiority in comparison with a group with no treatment regarding primary and secondary outcomes.We will perform regression analyses concerning impact of sociodemographic variables and psychopathology and the treatment outcome depending on the training condition.Subordinate, we are interested in mechanism-driven pathways of effective treatment with ICT in patients with regular binge eating behaviour. Thus, we exploratory investigate the pathways between the primary outcome and secondary outcomes, that also serve as predictors and moderators.

## Methods/design

The present study protocol is reported according to the SPIRIT checklist [13].

### Study design and setting

The MIND BINGES trial is a single centre clinical proof-of-principle double-blind RCT with three parallel arms.

Participants are recruited from the outpatient eating disorder service of the Medical University Hospital Tübingen, via study announcements in the media, via email lists of the University Tübingen, and individuals who have previously participated in eating disorder research studies at the Department of Psychosomatic Medicine and Psychotherapy and gave written consent to be informed about future studies. Interested participants receive verbal and written information material and are screened for inclusion and exclusion criteria through a standardized checklist. After providing written informed consent, the baseline assessment takes place. After completion of the baseline assessment, patients will be randomized in a 1:1:1 ratio to one of the three conditions. Outcomes will be measured at baseline (T0), at each training session (T1-T6), at end of treatment (T7) and at two follow-up timepoints, a four-week follow-up (T8) and a 3-months follow-up (T9).

### Study participants and eligibility criteria

The study population consists of individuals who report regular binge eating behaviour (at least 2 objective binge eating episodes per month within the past three months) and fulfil a diagnosis of BED, BN, OSFED or UFED according to the DSM-5 [4].

The eating disorder will be diagnosed by the *Eating Disorder Examination (EDE*; see 3.7.) [26], a standardized structured expert interview. OSFED/UFED is diagnosed, if one of the following cases occurs:The amount of objective binge eating episodes is below once per week during the last three monthsLess than three B-Criteria of binge-eating-episodes are fulfilled (Eating much more rapidly than normal; eating until feeling uncomfortably full; eating large amounts of food when not feeling physically hungry; eating alone because of feeling embarrassed by how much one is eating; feeling disgusted with oneself, depressed or very guilty afterwards)In case of potential BN: the amount of binge eating or purging is below once per week during the last three months or the individual does not suffer from body dysmorphia/dissatisfaction.

#### Inclusion criteria

Patient eligible for the trial must comply with all of the following at randomization:Age ≥ 18 yearsBMI > 18 kg/m.^2^Written informed consent

#### Exclusion criteria

Insufficient knowledge of German or English languageCurrent pregnancy or lactation periodCurrent or lifetime psychotic disorder, bipolar-I disorder, current substance dependence, current suicidalityPrevious bariatric surgerySevere somatic disorders (e.g. insulin resistance) which influence weight or eating behaviour and are not controlled by stable medicationSevere neurologic diseasespsychoactive medication that might interfere with cognitive functioning, e.g. neuroleptics, benzodiazepines, opioids as well as medication that might influence hunger/weight, e.g. GLP-1 receptor agonistsUncorrectable or impaired vision, ametropia, eye diseases which prevent from executing the task

### Interventions

Eligible patients who are randomized to one of the two training conditions receive six sessions of a food-related inhibitory control training within a two-weeks span and they will be randomly assigned to receive either feedback about their task performance in the food-related antisaccade task after each training session or receive no feedback. Patients being randomized to the control group will not receive any intervention within the two-weeks span.

#### Psychoeducation

A short psychoeducation (approximately 5–10 min) is provided by a trained psychologist to patients in the training condition with or without feedback. It consists of an overview on eating disorders that entail binge eating behaviour, as well as mechanisms of the inhibitory control training and the transfer of training effects to everyday life.

#### Inhibitory control training

The inhibitory control training is based on the principles of the antisaccade paradigm, an established experimental computer-based eye tracking task which is composed of two main components [5]: First, each trial starts with a central fixation cross which is thereafter succeeded by a stimulus presented slightly left or right from the cross in a peripheral screen position (see Fig. 1). If a novel stimulus appears in the peripheral visual field, as it is the case within the antisaccade paradigm, the reflexive reaction is to direct the gaze towards this stimulus, ergo, performing a prosaccade. The antisaccade paradigm demands to suppress this highly dominant behaviour which requires adequate inhibitory control. Previous studies have already shown that antisaccade performance is highly correlated with performance in other established tasks that assessed inhibitory control. In particular, brain networks involved in volitional behavioural and inhibitory control are activated during the antisaccade task [2, 27].

**Fig. 1 Fig1:**
[figure not shown]
Exemplary trial course of the food-modified antisaccade paradigm. Previously used by Max et al. [38]

In the food-modified antisaccade paradigm employed in a previous trial, we found that obese participants with BED demonstrated a higher prevalence of antisaccade difficulties. Additionally, participants exhibited greater challenges in averting their gaze from food images they had wrongfully looked at, supporting the assumption that binge eating behaviour is characterized by major impairments in inhibitory control and that this impairment might maintain maladaptive eating behaviours [50].

Based on this evidence, we previously conducted a trial with the food-specific inhibitory control training coupled with transcranial direct current stimulation (tDCS) [19], which showed promising results regarding improvement of inhibitory control as well as the amelioration of the eating disorder related pathology.

During the training session, patients with binge eating behaviour practice the suppression of a prepotent oculomotor response towards a peripheral food stimulus and with that we aim to reduce error rates, that is, the reduction of unwanted prosaccades towards food stimuli.

Analogue to Giel et al. [19], patients rate 40 colour pictures depicting high-caloric food concerning valence, appetite, liking, and wanting of the food item. Subsequently, the 20 highest-rated stimuli are individually chosen for the training period. During training, each picture is presented four times within one block, while presentation location on the screen (left/right) is counterbalanced. We present the stimuli in four blocks, resulting in 320 trials. Each trial starts with a central fixation cross (1250 ms), succeeded by a 200 ms interstimulus interval. Afterwards, the food picture is presented for 1000 ms. One group will receive feedback about their error rates after each training session, whereas the other group will not receive any feedback.

During task performance, the participant’s gaze is recorded using a iViewX Hi-Speed eye tracking system (SensoMotoric Instruments, 2010) with a sampling rate of 500 Hz and 0.25°–0.5° gaze position accuracy.

Hunger and mood are assessed at the beginning of every training session using visual analogue scales.

### Patient safety

Eye tracking is a non-invasive method used to record eye movements. We employ an infrared-assisted, video-based system in which a low-intensity infrared light is directed at one eye via a transparent mirror, producing a reflection point on the cornea. The device is CE-certified and used in accordance with its intended purpose. No safety risks are anticipated.

Regarding the interviews and questionnaires used, it is highly unlikely that they will cause any harm. However, in the event of unexpected emotional distress, the study will be discontinued immediately.

Potential (severe) adverse events will be documented by the experimenter as soon as reported during the study assessments or training sessions. The adverse event form contains following information [41]: detailed description of the event and affected patient,start and stop date and time; severity (yes/no); intensity (mild/moderate/severe); actions taken to manage the adverse event (yes/no); result of actions taken (fully healed/in the healing process/not healed/permanent damage/lethal/unknown); causality (given/probable/possible/unlikely/not given/not estimable). Study patients were encouraged to contact study staff in case of worsening of their condition at any time during the study.

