### Participant timeline

The participant timeline is depicted in Fig. 1.

Study duration for each patient comprises 14 weeks. After a baseline assessment (T0, 2 h) including a diagnostic assessment a randomization to either of the three study arms is conducted. Patients get randomized into a) 6 sessions of the food-modified antisaccade training (T1–T6, 20 min each) with feedback, b) 6 sessions of the food- modified antisaccade training (T1-T6, 20 min each) without feedback or c) without treatment during the two weeks. After this two-week span, a post-intervention assessment (T7, 75 min) will be conducted and thereafter a second post-intervention assessment four weeks after training termination (T8, 45 min) and a three-months follow-up assessment focusing on changes in eating disorder symptomatology via telephone (T9, 10 min) will be conducted. In total, the duration of the assessments for the ICT-conditions is around six hours and 10 min across nine appointments. For the waitlist control group, the four appointments take around 4 h and 10 min in total. Details on the investigated outcomes of each time point are presented at Table 1.

**Table 1 Tab1:** Schedule of enrolment, interventions, and assessments within the MIND Binges trial according to SPIRIT

		Baseline	Allocation	Intervention Period	Post-intervention I	Post-intervention II	12-week Follow-Up
**TIMEPOINT**		**T0**		**T1-T6**	**T7**	**T8**	**T9**
ENROLMENT:							
Eligibility screen		X					
Informed consent		X					
Randomization			X				
INTERVENTIONS:							
Inhibitory control training with Feedback							
Inhibitory control training without Feedback							
Waitlist control							
ASSESSMENTS (Instrument):							
Primary outcome:							
BE frequency in the last 4 weeks (EDE)		X				X	X
Secondary outcomes:							
Eating disorder pathology	Eating disorder pathology (EDE)	X				X	
	binge eating frequency in the last 7 days (Process analyses of impulsive behaviours)	X		X (only once per week)	X	X	
	Proportion of (partial) remission of BED (EDE)					X	X
General psycho-pathology	mental comorbidities (SCID-5-CV)	X					
	Depressive symptoms (BDI-II)	X			x	X	
Eating behaviour	Impulsive eating (TFEQ)	X			X	X	
Body Mass Index		X				X	X
Gender (GERAS)		x					
Quality of life (WHO-5)		X			X	X	
Stimulus valence ratings		x			x		
impulsivity	Inhibitory control (Antisaccade task performance)	X		X	X		
	Impulsive behaviours (Process analyses of impulsive behaviours)	X		X (only once per week)	X	x	

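### Adverse events are documented at training sessions that the waitlist arm does not have, so raw training-versus-waitlist event counts are open to unequal ascertainment of modest, uncertain size

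*Protocol article*

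**What the plan says.** The Patient safety section of the protocol article gives two routes by which an adverse event can come to light.

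- Scheduled contacts: "Potential (severe) adverse events will be documented by the experimenter as soon as reported during the study assessments or training sessions".
- Patient-initiated contact: "Study patients were encouraged to contact study staff in case of worsening of their condition at any time during the study". This is not limited to an arm or a visit, but it is worded for worsening of the condition, not for adverse events in general.

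The form records, among other items, "start and stop date and time; severity (yes/no); intensity (mild/moderate/severe"), as well as causality.

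The contact schedule differs by arm. Participant timeline gives the training arms "6 sessions of the food-modified antisaccade training (T1–T6, 20 min each) with feedback" (and the same number without feedback). Interventions says of the third arm: "Patients being randomized to the control group will not receive any intervention within the two-weeks span". For everyone, "After this two-week span, a post-intervention assessment (T7, 75 min) will be conducted", followed by T8 and T9. The Randomization section confirms that the waitlist arm also has the post-assessment and both follow-ups. In total: "For the waitlist control group, the four appointments take around 4 h and 10 min in total".

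The article names no adverse event comparison between arms among its aims, outcomes or statistical methods.

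**The concern.** The capture rule names training sessions as a place where events are recorded, and only two of the three arms have training sessions. If patients in all arms had events at the same true rate, the arms seen more often would tend to record more of them. The extra opportunity falls in the two weeks of training, when effects of the training, or deterioration while waiting, would first appear.

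The article states superiority over waitlist as an aim and says in the Discussion that the results should inform home treatment and app-based interventions. Even without a formal test, readers will compare adverse event counts by arm. An excess under training could then be partly an effect of contact frequency. Conversely, events during the waiting period could be under-recorded.

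**Working it through.** **1. Contacts per arm (Participant timeline, Randomization).** The stated durations are reproduced first.

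- Training: 120 + 6 × 20 + 75 + 45 + 10 = 370 min = 6 h 10 min, as stated.
- Waitlist: 120 + 75 + 45 + 10 = 250 min = 4 h 10 min, as stated, over T0, T7, T8 and T9 (four appointments, as stated).

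Post-baseline time points are T1-T9 = 9 for training and T7-T9 = 3 for waitlist. The article gives nine appointments in total for the training arms, while T0-T9 are ten time points. Less T0, its own count would be 8 versus 3. The two counts should be reconciled, but the point does not depend on which is right.

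| Period | Each training arm | Waitlist |
|---|---|---|
| Two-week period (T1-T6) | 6 | 0 |
| T7, T8, T9 | 3 | 3 |

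The whole difference lies in the first two weeks. Training with versus without feedback is 9 versus 9.

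**2. Upper bound: an event present before T1.** Assume that an event is reported with probability p at each later contact, independently. The chance that it is recorded at least once is 1 − (1 − p)^k for k contacts.

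| p | Training, k = 9 | Waitlist, k = 3 | Ratio |
|---|---|---|---|
| 0.05 | 37.0% | 14.3% | 2.6 |
| 0.10 | 61.3% | 27.1% | 2.3 |
| 0.20 | 86.6% | 48.8% | 1.8 |
| 0.50 | 99.8% | 87.5% | 1.1 |

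These are capture probabilities for an event that can be reported at every contact. They are not shares of patients with an event.

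**3. Onset spread over the study.** Assume uniform onset over 14 weeks, with T7 at week 2, T8 at week 6 and T9 at week 14. Then:

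- 2/14 of events start before T7 and have 9 contacts (training) or 3 (waitlist);
- 4/14 start between T7 and T8 and have 2 contacts in every arm;
- 8/14 start between T8 and T9 and have 1 contact in every arm.

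Giving every event of the first two weeks all nine training-arm contacts overstates the difference. With c(k) = 1 − (1 − p)^k, capture is [2c(9) + 4c(2) + 8c(1)]/14 for training and [2c(3) + 4c(2) + 8c(1)]/14 for waitlist.

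For p = 0.10, training: (2 × 0.6126 + 4 × 0.19 + 8 × 0.10)/14 = 2.785/14 = 19.9%. Waitlist: (2 × 0.271 + 4 × 0.19 + 8 × 0.10)/14 = 2.102/14 = 15.0%.

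| p | Training | Waitlist | Ratio |
|---|---|---|---|
| 0.05 | 10.9% | 7.7% | 1.4 |
| 0.10 | 19.9% | 15.0% | 1.3 |
| 0.20 | 34.1% | 28.7% | 1.2 |

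**4. Effect of the any-time route.** Suppose that it catches a share q of events in every arm. Capture becomes 1 − (1 − q)(1 − p)^k. For the early-onset event of step 2 at p = 0.10, the ratio falls from 2.26 to 0.729/0.490 = 1.49 at q = 0.3, and to 0.845/0.708 = 1.19 at q = 0.6.

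**The case against.** The strongest reply is that the article plans no between-arm comparison of harms. The safety section describes case documentation, and the exact way events are elicited may stand in a fuller protocol. The article does not say whether patients are asked or must volunteer. That is fair, and it limits the point to how event counts would be read. It does not remove it: the article does state where events are documented, and one of those places exists in only two arms.

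Three stronger readings are tempting, and the documents do not support them.

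- A reader might infer that events are captured only at scheduled contacts. The any-time route contradicts this. It covers worsening only and depends on the patient, so it reduces the imbalance without removing it.
- A reader might infer that harms cannot be compared between arms at all. The two training arms have identical schedules. All arms share T7, T8 and T9, event dates are recorded, and blinded raters conduct T8 and T9.
- A reader might infer that worsening in the waitlist arm goes unseen. The EDE binge count (T0, T8, T9) and the BDI-II (T0, T7, T8) are measured on the same schedule in all arms.

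It would also be wrong to read the threefold contact ratio as a threefold bias. The ratios in step 2 of the working need an event present before T1 that can be reported at every contact.

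**Conclusion.** The point holds in a limited form. As the capture rule is written, raw training-versus-waitlist adverse event counts are open to unequal ascertainment, because the training arms have six scheduled contacts in the two-week period and the waitlist arm has none. The likely direction is towards more recorded events under training.

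Under uniform onset and a reporting chance of 0.05 to 0.20 per contact, the capture ratio is about 1.4 to 1.2. It is larger for events that start right after baseline, and close to 1 if reporting is near certain or the any-time route works well. The onset pattern, the reporting chance and the independence between contacts are all assumptions. The documents give no figure for any of them.

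The primary analysis and the feedback comparison are not affected.

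**What to change.** Ask the same adverse event question, in the same words, in all arms at T7, T8 and T9. Each time it should cover the period since the previous common visit (T0 for T7, T7 for T8, T8 for T9). Base any training-versus-waitlist description of harms on those answers, and list events reported at T1-T6 separately. Because blinded raters conduct T8 and T9, the question should not mention training sessions.

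Optionally, tabulate by arm the number of patients whose EDE binge count (T8, T9) or BDI-II (T7, T8) is worse than at T0. This gives a symmetric measure of worsening from data already collected.

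The cost is about a minute at each of three existing visits, including the 10-minute T9 call, and one descriptive table. No visit or instrument is added.
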